### Data collection

Participants who are eligible and agree to participate in the study will be asked to complete an informed consent form on REDCap. After signing the informed consent form, participants will complete online questionnaires on REDCap. Participants will first complete a brief demographic survey (i.e. sex, sexual activity status) in order to receive tailored narratives. Participants will then complete a baseline survey (T0), view the materials for their assigned group (described above), and complete the post-intervention survey (T1). At 3-, 6-, and 9-month, follow-up surveys will be administered. These will be sent as links to participants via email or text message (depending on the preference of the participants). At the 3-, 6- and 9-month follow-ups, all participants who report initiating or completing the HPV vaccine series will be asked to consent to releasing their medical records on HPV vaccination from the clinic, pharmacy, or doctor’s office where they were vaccinated.

#### Qualitative interviews

After the 9-month follow-up, we will purposively select participants to take part in focus groups or in-depth interviews to understand (1) what made the intervention work in individuals who received at least one dose of the vaccine and (2) what made the intervention not work in individuals who did not initiate HPV vaccination. Focus groups and/or interviews will last approximately 60–90 min and will continue until data saturation is reached. Focus groups/interviews will be conducted virtually or in-person depending on participants’ schedule and preference.

### Data analysis

Prior to the inferential procedures, extensive descriptive statistical analyses will be performed on all variables of interest. Distributional assumptions will be evaluated, and if indicated, normalizing (such as log) transformations or robust procedures will be employed (e.g., for the continuous mediating variables). Appropriate procedures to assess the validity and reliability of the questionnaires will be used. As a general strategy for our primary analysis, an intention-to-treat (ITT) approach will be used.

#### Aim 1

Logistic regression analysis will be used to test the five comparisons on both the HPV vaccination initiation and completion rates (binary: yes vs. no), controlling for the stratification factors (gender, sexual activity status, and race/ethnicity) and additional covariates as appropriate [40]. While we do not anticipate a strong cluster (university) effect, we will explore the above comparisons using generalized linear mixed models (GLMMs) with a binomial outcome distribution with a logit-link function to account for potential within-university correlations. Each of the hypotheses in Aim 1 will be tested at a 2-sided 0.005 significance level to ensure statistical reproducibility by controlling the overall type I error rate at 0.05.

#### Aim 2

For *hypothesis 2.1*, we will examine if the impact of the intervention on outcomes at the 3-, 6-, and 9-month follow-ups are achieved through improved hypothesized mediators at the post-intervention and 3-month follow-up, respectively. We will use linear regression analysis in the intervention-mediator (a) path, and a logistic regression analysis in the intervention + mediator-outcome (b) path; the indirect (or mediation) effect will be defined by the product of the appropriate coefficients from the a and b paths [41, 42]. 95% bootstrap confidence intervals will be calculated to assess the significance of the indirect effects, using existing macros [43]. Both single- and multiple-mediator models will be tested [42]. To address *RQ1*, we will conduct analyses similar to those described in Aim 1 but focus on testing the interaction effects between the intervention condition and gender, a potential moderator of the intervention effect. Similar to the Aim 1 analyses, we will explore using linear mixed models (LMMs) for the path a analyses and GLMMs for the path b analyses to account for potential cluster (university) effects. All analyses performed in Aim 2 will use a 2-sided 0.05 significance level for hypothesis-generating (rather than confirmatory finding) purposes.

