### Settings and recruitment

We will recruit 1200 women and men in total. Participants will be recruited primarily from universities in the Houston metropolitan area— University of Houston, which has a large Hispanic student population; Texas Southern University, a historically Black university; Sam Houston State University, a Hispanic-serving institution; and Rice University, which has a large White and Asian American student population. Recruitment strategies will focus on mass e-mailing, posting fliers, in-person campus recruitment using student volunteers and staff recruiters, engaging student organizations and research labs, and in-class study announcements. We will also use various promotional items (e.g. bottled water, school supplies, sunscreen, etc.) that carry the study information to advertise. In addition, we will discuss recruitment strategies with student advisory boards and be guided by the input from these students. Participants will receive gift cards for completing surveys and participating in qualitative interviews. Participation retention is promoted through incentives after each study task, automated email reminders, and reminders from study staff via texts or phone calls.

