### Sample size calculation

Our sample size calculations are mainly based on hypothesis testing for both vaccination initiation and vaccination completion in Aim 1, with a two-sided alpha of 0.005 (= 0.05/10) (with a Bonferroni adjustment) for each test. This adjustment is used because Aim 1 has 10 tests in total, including five comparisons specified in hypotheses for each of the two HPV vaccination outcomes. The five comparisons are for two simple effects (i.e., written/video narrative + access vs. control), two marginal effects (i.e., written/video narrative vs. no narrative), and a main effect (access vs. no access). The assumed HPV vaccination rates for these comparison groups are calculated based on the expected vaccination rates inferred from the literature [20, 21, 33, 34] for the six groups (i.e., control, written narratives, video narratives, access only, access + written, and access + video): 12%, 20%, 22%, 20%, 40%, and 42% at 3-month follow-up for initiation, and 4%, 10%, 11%, 15%, 30%, and 32% at 9-month follow-up for completion, respectively. Post-attrition sample sizes used for power analysis represent the worst-case scenario and thus provide conservative estimates. Assuming 15% and 20% attrition at 3- and 9-month follow-ups, a total sample size of 1200 at baseline yields 1020 for analysis of vaccination initiation (1200*85%=1020) and 960 for completion (1200*80%=960), respectively. Sample sizes available per group for each comparison/test (written/video narratives + access vs. control, written/video narrative vs. no narratives, access vs. no access) are 170, 340, and 510 for HPV vaccination initiation and 160, 320, and 480 for HPV vaccination completion, respectively. Power analysis using nQuery 7.0 [35] shows that these sample sizes will have excellent power (82%~99%) to detect group differences in each of the 10 tests.

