#### Covariates

Potential covariates are demographic variables (age, sex, year in college, ethnicity, insurance coverage, household income, parents’ level of education) and sexual history (sexually active or not).

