**Secondary Outcomes**:								
Self-Efficacy			X		X	X	X	
Intention to Initiate Vaccination			X		X	X^b^	X^b^	X^b^
Intention to Complete 3 Doses of the HPV Vaccine			X		X	X	X	X^c^

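### The primary logistic model does not name baseline (T0) intention to vaccinate, which leaves some likely power unused on the narrative comparisons

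*Protocol article*

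**What the plan says.** **Model.** Data analysis, Aim 1, specifies logistic regression for five comparisons on each of two outcomes, initiation and completion. It controls for gender, sexual activity status and race/ethnicity, and allows additional covariates without naming them.

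**Candidate covariates.** The Covariates section begins "Potential covariates are demographic variables". It lists age, sex, year in college, ethnicity, insurance, household income and parental education, and adds sexual history. Intention, self-efficacy and university are not listed.

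**Baseline intention.** Table 2 marks "Intention to Initiate Vaccination", intention to complete three doses, and self-efficacy at T0, with no footnote restricting who answers at that time point. Data collection places the T0 survey before participants view their assigned material. Secondary outcomes says that the intention items concern starting within 3 months and completing the series; it uses the post-intervention values as outcomes.

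**University.** Settings and recruitment says "Participants will be recruited primarily from universities in the Houston metropolitan area" and names four. Randomization is not stratified by school. Aim 1 says "While we do not anticipate a strong cluster (university) effect, we will explore the above comparisons using generalized linear mixed models (GLMMs".

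**Power.** Sample size calculation works "with a two-sided alpha of 0.005 (= 0.05/10) (with a Bonferroni adjustment) for each test" and reports 82% to 99% over ten tests.

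**The concern.** In a randomised comparison analysed by logistic regression, adjusting for a strongly prognostic baseline variable raises the power of the treatment test. A person's stated intention, before any exposure, to start or complete the series is a natural candidate for such a variable here, on the plan's own behavioural theory. The candidate list instead consists of demographics and sexual history. The open clause would allow intention to be added later, but nothing commits the analysts to it. A covariate set that is still open when ten confirmatory tests are run is also less useful than one fixed beforehand.

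What is at stake is power for the narrative effects. These have the least reserve at a per-test alpha of 0.005, above all written versus no narrative on completion. There is a second use. Handling of missing data ties the validity of the observed-data analysis to missingness depending only on variables in the model, and worries that people who do not vaccinate may leave early. T0 intention is a baseline variable that could carry that dependence.

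**Working it through.** **1. Reproduce the plan's figure.** Inputs from Sample size calculation:
- completion rates of "4%, 10%, 11%, 15%, 30%, and 32% at 9-month follow-up for completion", in the order control, written, video, access, access + written, access + video;
- "Assuming 15% and 20% attrition at 3- and 9-month follow-ups", so 1200 × 0.80 = 960 analysed, 160 per cell;
- alpha 0.05/10 = 0.005, two-sided, z = 2.807.

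The marginal comparison pools two cells, so it has 2 × 160 = 320 per side. No narrative: (4 + 15)/2 = 9.5%. Written: (10 + 30)/2 = 20%. Mean rate: 14.75%.

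Pooled two-proportion formula: power = Φ{[d√n − z√(2p̄q̄)] / √(p₁q₁ + p₂q₂)}.
- d√n = 0.105 × √320 = 1.878
- z√(2p̄q̄) = 2.807 × √(2 × 0.1475 × 0.8525) = 1.408
- √(0.095 × 0.905 + 0.20 × 0.80) = 0.496
- Φ[(1.878 − 1.408)/0.496] = Φ(0.949) = 82.9%

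This is the lowest of the ten and agrees with the stated 82%. The other narrative tests are video versus none on completion (92.0%) and, from the initiation rates "12%, 20%, 22%, 20%, 40%, and 42% at 3-month follow-up for initiation" with 340 per side, written (94.0%) and video (98.3%). The access and combined-versus-control tests are all at about 99.9% or more. The calculation takes no credit for covariates.

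**2. Add baseline intention.** Its prognostic strength is not in the documents, so it is assumed, as log-odds per SD. The method is simulated six-arm trials at the planned completion rates, analysed with a Wald test in a main-effects logistic model. Stratification factors were not simulated. That model also contains access, so its unadjusted power of about 85–86% differs a little from the formula value above.

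Weakest test (completion, written versus none), intention alone, 3,000 trials per setting:

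| Log-odds per SD | OR per SD | Without | With | Gain (points) |
|---|---|---|---|---|
| 0.5 | e^0.5 = 1.6 | 85.4% | 87.4% | 2.0 |
| 0.8 | e^0.8 = 2.2 | 86.0% | 89.4% | 3.4 |
| 1.1 | e^1.1 = 3.0 | 85.3% | 91.2% | 5.9 |

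A repeat of these settings gave about 86% rising to 87%, 90% and 92%. A further simulation (5,000 trials per setting) added intention and university together, over a wider range and with modest site differences:

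| Log-odds per SD | Written vs none | Video vs none |
|---|---|---|
| 0.5 | 84.9% → 86.8% | 94.0% → 94.8% |
| 1.0 | 85.6% → 90.7% | 94.0% → 96.7% |
| 1.5 | 86.3% → 95.3% | 93.9% → 98.6% |

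If intention has no prognostic value and sites do not differ, adding both costs essentially nothing (85.5% without, 85.3% with). Access and combined-versus-control tests stay at about 99.8% or more throughout.

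**3. Separate out university.** Site differences are also an assumption, with four equal sites and no intention effect. University alone moves the weakest test from 85.4% to 86.0% at a site SD of 0.2 log-odds, and from 84.9% to 86.8% at 0.5. The gain is 0.6 and 1.9 points.

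**4. Random effect from four sites.** Mean completion rate: (4 + 10 + 11 + 15 + 30 + 32)/6 = 17%. With 960/4 = 240 per site, the sampling variance of a site logit is s² = 1/(240 × 0.17 × 0.83) = 0.0295. With true site variance τ², the maximum-likelihood estimate is zero when a χ² on 3 df falls below 4s²/(s² + τ²).
- τ = 0.2: threshold 1.70, probability about 36%
- τ = 0.3: threshold 0.99, about 20%
- τ = 0.5: threshold 0.42, about 6%

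With the weak site effect that the plan expects, the mixed model would often reduce to the model without university.

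**The case against.** **Nothing is excluded.** A reader might infer that the plan leaves intention and university out of the primary model. The open clause in Aim 1 bars neither, and the full covariate list is commonly settled in an analysis plan that is not shown. This stands against any claim of omission. What remains is that the article does publish a candidate list, and the baseline measures closest to the outcomes are not on it.

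**The planned power is already met.** This stands. All ten tests reach the stated range without the change, and a sizeable gain is confined to the narrative tests.

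**The gain rests on an assumed prognostic strength.** This also stands, which is why a range is given.

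**Precision.** A reader might infer a tighter odds ratio. Adjustment in logistic regression moves the target to a conditional odds ratio, and the standard error of its logarithm does not shrink. The gain is in power.

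**University.** A reader might infer that leaving it out biases the comparison, or that campuses differ in clinics or health centres. Participants are randomised individually, so there is no bias. The documents describe campus differences only in student mix and type of institution, and race/ethnicity is both a stratification factor and a model covariate. The mixed model is exploratory and not the primary analysis, and its site variance is not a target of inference; if that variance is estimated as zero, the primary logistic result is recovered.

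**Conclusion.** The point holds as a modest, nearly free improvement. The plan does not name T0 intention, although it is measured in everyone before exposure and asks about the behaviours that define both primary outcomes. Over an assumed 0.5 to 1.1 log-odds per SD, the weakest test gains about 2 to 6 points of power, or up to about 9 at 1.5. The other narrative tests gain less, and the access and combined tests gain almost nothing. No figure exists for the added power from self-efficacy, so it is suggested only for imputation.

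The documents do not support reading this as a fault in the sample size calculation or as a source of bias. University is minor, at about 0 to 2 points.

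**What to change.** 1. In the Aim 1 model, name T0 intention as a linear covariate beside the three stratification factors: the item on initiating for the initiation outcome, and the item on completing for the completion outcome. Fix this before any comparison by arm is seen.
2. Include T0 intention and T0 self-efficacy in the multiple-imputation model.
3. State that the reported odds ratio is conditional on intention.
4. Optionally, if university is to be accounted for, use fixed indicators for the participating schools and keep the mixed model as a sensitivity analysis. Recruitment is described as primarily, not only, from the four named schools, so any further school needs its own indicator or a stated grouping.

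The cost is a few lines of analysis-plan wording and one more parameter per model, or about three more with university. Intention and self-efficacy are already collected, and enrolment at a participating school is an eligibility criterion. No change to sample size or data collection follows.

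### Holm's step-down procedure would meet the plan's own 0.05 family-wise target with more power for the narrative tests than a fixed 0.005 for each of the ten Aim 1 tests

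*Protocol article*

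**What the plan says.** The sample size section counts the family: "Aim 1 has 10 tests in total, including five comparisons specified in hypotheses for each of the two HPV vaccination outcomes". The five comparisons are two simple effects (each narrative with access versus control), two marginal effects (each narrative versus no narrative) and the main effect of access. The trial is sized "with a two-sided alpha of 0.005 (= 0.05/10) (with a Bonferroni adjustment) for each test", and every one of the ten tests is reported to have 82% to 99% power.

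The Data analysis section, under Aim 1, carries the same level into the decision rule: "Each of the hypotheses in Aim 1 will be tested at a 2-sided 0.005 significance level to ensure statistical reproducibility". The declared purpose is "controlling the overall type I error rate at 0.05". The article mentions no step-down or other sequential procedure. The two sections agree with each other.

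**The concern.** The rule holds every test at 0.05/10 even after other hypotheses in the family have been rejected. Holm's procedure orders the ten p-values and compares the smallest with 0.05/10, the next with 0.05/9, and so on, stopping at the first failure. It controls the family-wise error at 0.05 under any dependence between the tests, and it rejects everything that Bonferroni rejects and sometimes more. The plan's stated goal is therefore available at a lower price in power.

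The price falls on Hypothesis 1.2, that narratives improve vaccination over CDC information. Its four tests (written and video, on initiation and completion) are the least powered in the family at the planned rates. They are also the tests for which the relaxed thresholds would matter.

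**Working it through.** **Inputs, all from the sample size section.** The group order is control, written, video, access, access + written, access + video.
- Initiation: "12%, 20%, 22%, 20%, 40%, and 42% at 3-month follow-up for initiation".
- Completion: "4%, 10%, 11%, 15%, 30%, and 32% at 9-month follow-up for completion".
- "Assuming 15% and 20% attrition at 3- and 9-month follow-ups" leaves 1020 and 960 participants, i.e. 170 and 160 per group.

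**Rates per comparison.** Marginal rates are simple averages of the group rates. For completion, written narrative is (10 + 30)/2 = 20%, no narrative is (4 + 15)/2 = 9.5%, and video is (11 + 32)/2 = 21.5%. Access is (15 + 30 + 32)/3 = 25.7% and no access is (4 + 10 + 11)/3 = 8.3%. Initiation is treated in the same way.

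**Step 1: reproduce the stated power.** With n per side, p̄ = (p1 + p2)/2 and z = 2.807 (two-sided 0.005),

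power = Φ{ [ |p1 − p2| − z·√(2p̄(1 − p̄)/n) ] / √([p1(1 − p1) + p2(1 − p2)]/n) }.

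For written narrative on completion, p1 = 0.20, p2 = 0.095, n = 320 and p̄ = 0.1475:
- z·√(2 × 0.1475 × 0.8525/320) = 2.807 × 0.02803 = 0.0787
- √((0.1600 + 0.0860)/320) = 0.0277
- (0.105 − 0.0787)/0.0277 = 0.95, so power is 82.9%.

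This is the smallest of the ten and reproduces the stated 82%.

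**Step 2: Holm's thresholds.** The sequence is 0.05/10 = 0.005, 0.05/9, ..., 0.05/1. Six tests have at least 99.9% power at 0.005. Once those six are rejected, the smallest of the four remaining p-values is compared with 0.05/4 = 0.0125, then 0.05/3 = 0.0167, 0.025 and 0.05.

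**Step 3: compare the two rules by simulation.** There were 40,000 trials at the planned rates, with pooled z-tests. Completers were taken as a subset of initiators; this is an assumption, since the article gives no joint distribution.

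| Test | Rates | n per side | Formula, 0.005 | Simulated, fixed 0.005 | Simulated, Holm |
|---|---|---|---|---|---|
| Initiation, written vs none | 30% v 16% | 340 | 94.0% | 94.5% | 98.7% |
| Initiation, video vs none | 32% v 16% | 340 | 98.3% | 98.6% | 99.7% |
| Completion, written vs none | 20% v 9.5% | 320 | 82.9% | 84.4% | 96.7% |
| Completion, video vs none | 21.5% v 9.5% | 320 | 92.0% | 93.1% | 98.8% |
| Other six tests | – | – | at least 99.9% | at least 99.9% | at least 99.9% |

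The simulated power for the weakest test lies about 1.5 points above the normal approximation at the same level (84.4% against 82.9%). Holm's 96.7% should be read with that in mind: the formula gives 96.4% for this test at an unadjusted 0.05, the threshold it faces when the other nine have been rejected.

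**Step 4: error rate.** With no effect anywhere (200,000 trials per setting), the family-wise error was 3.6% with all groups at 12% initiation and 4% completion, and 3.8% at 25% and 15%. It was identical under the two rules in both settings.

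**Step 5: effects smaller than planned.** Both scenarios are assumptions.
- All differences from control at 75% of plan: written narrative on completion goes from 61% to 84%.
- Effects additive on the risk scale, in place of the larger combined effects in the plan. For completion, access + written is 4 + 6 + 11 = 21% and access + video is 4 + 7 + 11 = 22%. For initiation they are 12 + 8 + 8 = 28% and 12 + 10 + 8 = 30%. Written narrative on completion goes from about 30% to 52%, and on initiation from about 42% to 62%.

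**The case against.** The strongest reply is that nothing here is wrong. Fixed Bonferroni is valid under any dependence, it is prespecified, the two sections agree, and the trial was sized for it with at least 82% power on every test. All of that stands. A reader might infer that the plan contains an error or falls short of its own power claim; the documents do not support this, because the stated range reproduces.

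A reader might also infer that Bonferroni is wasteful because the ten tests are strongly correlated, and that Holm recovers that loss. This does not hold. From the shared groups, null correlations within an outcome run from 0 (access main effect with either narrative marginal effect) to 0.71 (a simple effect with its own marginal effect). The article states no correlations, and those across outcomes depend on the nesting assumption. More importantly, Holm does not use correlation: the slack that correlation leaves below 0.05 is the same under both rules. Recovering it would need a resampling or joint-distribution method.

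The chance that all ten tests succeed rises from 79% to 96% at the planned rates. That figure should not lead the argument, because the article sets no all-ten success criterion and speaks of power for each test. Per test, six gain essentially nothing, video on initiation gains about one point, and three gain materially.

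Nor does Holm rescue optimistic effect assumptions: at about 52% in the additive scenario, written narrative on completion would still be underpowered.

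Finally, Holm makes the initiation results depend on the completion results. An initiation p-value above 0.005 cannot be settled until the 9-month tests exist. This is a real cost but a small one. The Discussion expects data collection to end by March 2026 and the main results to be submitted by 2027, and any initiation test at or below 0.005 stands under either rule.

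**Conclusion.** The point holds as a cheap improvement in efficiency, not as a correction. The current rule meets the 0.05 target, but it forgoes power that Holm would provide at the same family-wise guarantee and sample size. At the planned rates the gain is about 12 points for written narrative on completion (84.4% to 96.7%), 6 for video on completion (93.1% to 98.8%) and 4 for written on initiation (94.5% to 98.7%). It is larger when effects are smaller: about 22 points for written narrative on completion in the additive scenario.

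That Holm never rejects less and controls the error under any dependence requires no assumption about the data. The size of the gain rests on the plan's assumed rates and attrition, on completers being nested in initiators, and on unadjusted two-proportion tests standing in for the planned covariate-adjusted logistic regression.

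**What to change.** In the Data analysis section, under Aim 1, replace the sentence that sets 0.005 for each hypothesis with: the ten Aim 1 p-values are tested by the Holm step-down procedure at a two-sided family-wise alpha of 0.05. Keep the 0.005 calculation in the sample size section and label it as the conservative planning figure.

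The change is one sentence and needs no further participants or data. It must be made and dated before unblinding, since choosing Holm after seeing the p-values would not be credible. Two consequences should be written down with it:
- Initiation tests with p above 0.005 are declared only once the 9-month completion p-values are available.
- 99.5% confidence intervals can still be shown, but such an interval may include no effect for a hypothesis that Holm rejects. The plan should say that the Holm result governs the claim.
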